**Figure 1. f1:**
[figure not shown]
Study Flow Diagram.

**Table 1. T1:** Schedule of study enrolment, interventions and assessment.

**Timepoint**	-T _3_	-T _2_	-T _1_	T _0_	0–2 week	2–12 weeks	12 week	6 months
Enrolment								
GP enrolment	x							
Physio enrolment	x							
Pt enrolment				x				
Intervention								
GP training		x						
Physio training		x						
GP ‘Enhanced Consultation’			x					
‘Best practice’ Physio Session					x			
Assessment								
*Quantitative Data Collection*								
GP & Physio descriptive data		x						
Pt baseline descriptive data				x				
Pt clinical & feasibility outcomes				x			x	x
GP & Physio follow-up questionnaire								x
*Qualitative Data collection*								
Pt Interviews							x	x
GP & Physio Interviews								x

GP, general practitioner; Physio, physiotherapist; Pt, patient; T
_0_, baseline.

This study is located within the feasibility and piloting stage of the MRC’s framework that provides guidance on the design and development of complex interventions
^
35
^. A single arm feasibility study was chosen rather than a comparative design because the main focus was to resolve uncertainties about the acceptability and feasibility of the intervention itself, and its mode of delivery. A non-randomised design provided an opportunity to test the intervention with a greater number of HCP and patient participants. According to the MRC’s guidance on the development and evaluation of complex healthcare interventions, a feasibility study need not be a scale model of a future planned evaluation but instead is an opportunity to examine the key uncertainties that have been identified during development
^
35,
55
^.

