^. Patients will also receive verbal and written educational information on their knee pain prior to enrolling in the study, representing an enhanced version of usual care. As part of usual care for people attending their GP with knee pain, patients are routinely assessed and educated about their condition
^
30
^, therefore this intervention does not represent any risk or burden to patients who ultimately do not enrol in the study and decline to participate in data collection. GPs will also explain that study participation involves attending a ‘best practice’ session of physiotherapy in UHK and this not affect the patient’s access to a routine physiotherapy appointment (typically 6 to 12 months wait for a public appointment), should patients also wish to avail of this. Having discussed the study, GPs will seek written consent from interested patients to forward their contact details to the research team. The PI will contact prospective participants by telephone to answer any questions, confirm their eligibility and that they have read the written study information. Consenting patients will be enrolled in the study, following receipt of a signed consent form either written or electronically. An emailed link to the baseline questionnaires will follow. Participants will also indicate if they are amenable to being contacted for a post-intervention qualitative interview. They will sign a subsequent consent form before this interview is conducted.

If a potential participant ultimately declines to participate, having discussed the study with the researcher, they will still have the opportunity to avail of the ‘best practice’ physiotherapy intervention, but no study data will be collected. 

Patients will be eligible for this study if they are:

Attending their GP with an episode of non-traumatic knee pain.Have knee pain attributed to a diagnosis of DMT and early OA, made via a GP clinical assessment and based on features agreed by expert consensus
^
59,
60
^.Aged between 35 and 69 years inclusive. Inclusion of people aged 35 years or older is based on expert consensus, clinical practice guidelines and several RCTs investigating surgery for people with degenerative meniscal lesions also use this age cut-off
^
10,
15,
59,
61
^.

Criteria for exclusion are: (i) fulfilling the European League Against Rheumatism (EULAR) clinical classification criteria (Proposition No. 5) for knee OA, which reflect more established OA disease
^
49

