	GPs receive a study folder handbook detailing study procedures (e.g. recruitment, intervention delivery, referral to ‘best practice’ physiotherapy session). Educational materials will include copy of PowerPoint slides, communication tips, links to patient educational videos on weight maintenance, load management etc. Physiotherapists receive a training manual detailing components of the ‘best practice’ physiotherapy session, a pre-recorded webinar on addressing patient fears and misconceptions about their knee pain, and educational materials and self-management resources. Participating patients receive a Patient Advice Leaflet, with illustrated home exercises and video links, written exercise programme with progressions and regressions, a goal setting and action plan worksheet, physical activity logbook and additional educational handouts on management of flare-ups etc, as appropriate.
4.	Who provided
	Participating GPs deliver the ‘enhanced consultation’ to potential patient participants, while participating musculoskeletal physiotherapists provide the ‘best practice’ physiotherapy session. A clinical specialist physiotherapist and researcher ([name]) facilitates the training workshops to participating GP and physiotherapists, with support from clinical and academic physiotherapy colleagues.
5.	How
	Training workshops are delivered to GPs in small groups (n=6 to 8), either as in-practice training, or with several GPs practices together. Participating patients receive an ‘enhanced consultation’ during a routine consultation with their GP and the ‘best practice’ session will be one-to-one with the physiotherapist.
6.	Where
	The location for GP training varies, either in a GP practice or a rented meeting room to facilitate GPs from several practices. Physiotherapist training is held in the outpatient clinic of a physiotherapy department in a publicly funded hospital, where the ‘best practice’ physiotherapy intervention is delivered. GPs deliver an ‘enhanced consultation’ in their practice.
7.	When and how much
	Participating GPs and physiotherapists receive their respective 2-hour training workshop on enrollment into the study. Patient participants receive an ‘enhanced consultation’ with their participating GP when they present to their GP practice with knee pain. A single one-hour ‘best practice’ physiotherapy session is delivered within 2 weeks of the GP consultation.
8.	Tailoring

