**physiotherapist training workshop** will be delivered by two members of the research team ([name] and [name]). This two-hour session will include review of knee joint assessment, exploring individual patient beliefs and expectations about their knee pain, delivering tailored patient education, exercise prescription, self-management skills and techniques to maximise patient adherence to a management plan. The workshop will focus on training physiotherapist to adopt a collaborative approach during the ‘best practice’ session that focuses on listening to the patient, understanding their individual concerns and worries, delivering information to reduce fear and address misconceptions, before designing a plan focused on their own goals and interests and delivering tailored education and an exercise programme. This session will be accompanied by a training manual to ensure standardisation of training and material delivered. While training content for clinicians is standardised, physiotherapists will be encouraged to individualise the patient sessions. In addition to the training workshop, physiotherapists will listen to a thirty-minute pre-recorded webinar on addressing common patient misconceptions and beliefs about knee pain. The training manual will include written guidance on the core components of the ‘best practice’ session and additional educational resources on knee pain and communication tips.

**
*Patient intervention.*
** The patient intervention consists of an ‘enhanced consultation’ with their GP and a ‘best practice’ physiotherapy session delivered within two weeks of their GP visit. The patient intervention will be guided by clinical guidelines and include education, exercise and where appropriate, weight management advice
^
26
^. A core focus will be boosting self-management skills and empowering patients with information and resources to manage their symptoms, without the need for inappropriate imaging or surgical consultations. These intervention components will be delivered briefly during the GP consultation through verbal and written information, and addressed more comprehensively during the physiotherapy ‘best practice’ session and using printed and video resources.

a)The ‘

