^. Questions on the seven component constructs (affective attitude, burden, ethicality, intervention coherence, opportunity costs, perceived effectiveness and self-efficacy) are adapted for the KNEE-DEeP study and each rated using a five-point Likert scale ranging from ‘Strongly disagree’ to ‘Strongly agree’.

Qualitative data collection with HCPs will explore the acceptability of the HCP intervention and their experience of the training workshops. How acceptable the HCPs perceived the patient intervention to be will also be discussed during these interviews. Patient interviews to explore acceptability will focus on understanding if patients liked and valued the various components of the KNEE-DEeP intervention as it was delivered.

**
*KNEE-DEeP fidelity.*
** Fidelity is the degree to which an intervention was implemented as the developers of the intervention intended
^
71,
75
^. Fidelity of delivery and receipt of the KNEE-DEeP intervention will be assessed using quantitative and qualitative data collection. While it is not practical to measure directly GPs delivery of the components of the ‘enhanced consultation’, an indirect or proxy measure will be used in the form of two checklists. GPs will indicate their delivery of the four components of the ‘enhanced consultation’ on a checklist as part of completing the ‘best practice’ physiotherapy referral form. Patient participants will complete a checklist as part of their baseline questionnaire, indicating receipt of these intervention components during the GP consultation. At the end of each session, physiotherapists delivering the KNEE-DEeP ‘best practice’ session will complete treatment logs. This consists of a checklist documenting the key session components (e.g., clinical assessment, exploring beliefs, aspects of patient education, self-management skills, goal setting etc).

Qualitative data on aspects of fidelity, including delivery and receipt of HCP training, delivery of the patient intervention by HCPs and enactment of the clinical intervention by patients, will be gathered during interviews with a subset of patients and HCPs.

**
*Preliminary efficacy.*
** Preliminary efficacy will be assessed by the change in the primary clinical outcome measure of self-reported knee-function. All primary and secondary clinical outcome measures are described below.

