**Quantitative data collection and analysis**

Data relating to study procedures (recruitment, retention etc) will be collected throughout. Participants will be invited to complete the baseline and follow-up questionnaires via an online link to Microsoft (MS) Forms. Data from MS Forms will be stored electronically on UL’s secure OneDrive cloud storage, exported to Microsoft Excel. Participants will also have the option of completing paper questionnaires, if this is their preference. Data from paper based questionnaires will be transferred by a researcher to Microsoft Excel. Demographic data from GPs and physiotherapists will be collected following study enrolment at the training workshops by paper questionnaire.

Follow-up questionnaires will be sent to patient participant at 12 weeks and 6 months. For those who do not respond, at least one reminder will be sent, via email or by post. For those who do not respond to the reminder, a telephone follow-up will be used to contact participants. Participating GPs and physiotherapists will complete a follow-up questionnaire at the conclusion of recruitment and intervention delivery.

Participants’ characteristics and implementation outcomes will be described using descriptive statistics such as means, standard deviations and ranges for quantitative variables, and counts and proportions for categorical variables. Descriptive statistics will also be used to measure change in outcome measures from baseline to 12 weeks and 6-month time-points and results will be treated as exploratory. Means and confidence intervals of the KOOS-PS will be calculated in order to inform the sample size calculation for a future definitive RCT.

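### Baseline follows the GP enhanced consultation, so change from baseline misses any effect of that consultation before T0, and a baseline completed after the physiotherapy session is not guarded against

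*Protocol article*

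**What the plan says.** All references are to the protocol article.

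- **Intervention.** Under Patient intervention: "The patient intervention consists of an ‘enhanced consultation’ with their GP and a ‘best practice’ physiotherapy session".
- **Order of the GP part and enrolment.** Under Recruitment and participants (patients with knee pain): "Patients will also receive verbal and written educational information on their knee pain prior to enrolling in the study". After the research team's telephone call and receipt of signed consent, "An emailed link to the baseline questionnaires will follow".
- **Schedule.** Table 1 marks the row "GP ‘Enhanced Consultation" in column -T1, patient enrolment and baseline data at T0, and the row "Best practice’ Physio Session" in the 0–2 week column.
- **Session timing.** Table 2, item 7: "A single one-hour ‘best practice’ physiotherapy session is delivered within 2 weeks of the GP consultation". Under GP intervention, the GP sends the referral form by email straight to the physiotherapy department.
- **Consent.** Ethics and informed consent provides for several days between receiving study information and deciding. Patients who decline may still attend the session.
- **Fidelity.** "Patient participants will complete a checklist as part of their baseline questionnaire, indicating receipt of these intervention components during the GP consultation".
- **Use of the data.** Objective 8 concerns the size and spread of change in the clinical outcomes. The Preliminary efficacy paragraph uses change in self-reported knee function (KOOS-PS). The analysis section says "Descriptive statistics will also be used to measure change in outcome measures from baseline to 12 weeks and 6-month time-points" and treats these results as exploratory.

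**The concern.** A baseline for a before-and-after summary should come before the thing whose effect is being described. Here the first half of the patient intervention has already been delivered when T0 is measured: clinical assessment, educational messages, leaflet with starter exercises, and agreed treatment plan. A reader who sees change from baseline under the label preliminary efficacy will take it as change with KNEE-DEeP as a whole. It is change after the GP consultation.

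A second weakness is practical. The path to the session and the path to the baseline form start at the same GP visit and then run separately. The article states no rule that the form must be completed before the session starts. For a slow responder, baseline could follow both components, and the starting point of change would then differ between patients.

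At stake is the reading of Objective 8 and of the KOOS-PS summaries that are meant to inform a later trial's sample size. The acceptability and fidelity findings do not depend on it.

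**Working it through.** The article gives no power, effect size, standard deviation or bias figure on this point, so there is nothing to reproduce. The check is of sequence, followed by a day count.

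**1. Order of events**

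| Event | Position in Table 1 | What the text adds |
|---|---|---|
| GP enhanced consultation | -T1 | Education is given before enrolment |
| Enrolment and baseline data | T0 | Link is sent after the call and signed consent |
| Physiotherapy session | 0–2 week column | Two weeks counted from the GP visit |

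Two further statements confirm that T0 comes after the consultation. The baseline form asks which consultation components the patient received. The several days allowed for the decision also exclude a baseline on the day of the GP visit.

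**2. What the change score contains.** Let Ypre be the score before the consultation, Y0 the score at T0 and Y12 the score at 12 weeks.

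Y12 − Ypre = (Y0 − Ypre) + (Y12 − Y0)

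Only Y12 − Y0 is observed. Y0 − Ypre is lost, and the article gives nothing from which to estimate it. If the consultation helps at once, reported change is smaller than change since before the consultation. Effects of the advice, leaflet and starter exercises that appear after T0 remain in Y12 − Y0.

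**3. Outcomes most exposed.** The GP messages cover diagnosis, a positive but realistic prognosis, and the safety and benefits of exercise. GPs are also asked to foster positive attitudes to exercise ahead of the physiotherapy session, which is the interval in which T0 falls. FABQ and PSEQ-2 are measured at baseline, 12 weeks and 24 weeks (Table 3), so they have change scores and are the most plausibly affected. KOOS-PS could be affected through the starter exercises, but a shift within days is less plausible.

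**4. The two-week windows.** Put the GP visit at day 0, baseline at day B (B ≥ 0) and the session at day S. The text requires S ≤ 14. If S follows B, as Table 1 intends, then S − B ≤ 14 − B ≤ 14. A session that meets the text's limit therefore also meets Table 1's 0–2 weeks from T0.

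**5. Time left for the baseline form.** The article does not quantify several days; 3 to 7 is an assumption. The days left cover the call, return of consent, sending of the link and completion of the form.

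- Session on day 14: 14 − 3 = 11 days, or 14 − 7 = 7 days.
- Session on day 7, as an example of earlier booking: 7 − 3 = 4 days, or 7 − 7 = 0 days.

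Because the GP refers directly and decliners may attend, the session does not depend on enrolment. A baseline completed after it is possible under the text.

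**The case against.** The strongest reply is that the order is deliberate and openly stated. Eligibility rests on the GP's assessment, consent needs several days, and the baseline form carries the checklist of components received. Under this consent route a study questionnaire before the consultation is not obtainable. This stands: the article does not misstate the order, and the remedy is to describe T0 correctly, not to move it.

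The next reply is that Table 1 puts baseline before physiotherapy, and that a rule on booking may sit in the full protocol or in the study folder given to GPs. This stands in part. The planned order is clear, so a post-session baseline is a lapse that nothing in the article prevents, not something the plan calls for.

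A reader might also infer that Table 1 and the text contradict each other because one counts from T0 and the other from the GP visit. They do not: step 4 of the working shows that the text's limit is the stricter one and implies the other.

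Last, the consequence is limited. The study is single-arm, effectiveness is not its primary aim, change is the last of eight objectives, and uncontrolled change cannot be attributed to the intervention wherever T0 falls. That limits the weight of the point. It does not correct the preliminary efficacy label, which leaves the reader unaware of where change begins.

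**Conclusion.** The point holds in a limited form. Even if the plan is followed exactly, change from baseline excludes any effect of the GP consultation before T0, most plausibly on FABQ and PSEQ-2. In addition, a baseline completed after the physiotherapy session is possible and unguarded. How often that would happen, and how large any bias would be, cannot be computed from the article. The day counts rest on the assumed 3 to 7 days for the decision.

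Three stronger readings are tempting but unsupported:

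- That change from baseline leaves out the GP component altogether. Only the part before T0 is lost.
- That a late baseline gives a change excluding the whole intervention. The session produces a home exercise or activity plan that is carried out afterwards, so effects of both components can still appear after such a baseline.
- That change in recovery expectations is biased. They are collected at baseline only (Table 3), so no change score exists.

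The correction should be made because it is cheap. It does not threaten the study's main feasibility aims.

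**What to change.** 1. **Wording.** Describe T0 as a post-consultation baseline. State Objective 8 and preliminary efficacy as change after the GP consultation.
2. **Dates and order.** Record the dates of the GP consultation, the baseline form and the physiotherapy session. The referral form and the physiotherapist's treatment log already exist and could carry two of them. Have any outstanding baseline form completed before the session starts, for example on paper at check-in.
3. **Analysis.** Flag baselines completed after the session, leave them out of the main change summary, and show results with and without them.

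The cost is a few sentences, three date fields and a paper form at reception. The downside is a narrower claim and possibly a few lost baselines from a target of 36 patients. Patient recruitment began in June 2024 with about six months anticipated, and this version is dated December 2024, so the check-in form may reach few patients. The wording, the dates and the two-way summary can still be applied to everyone whose dates can be recovered.

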### Intervention for health care professional and patient participants

The KNEE-DEeP intervention (
Figure 2) is a complex intervention designed to improve the uptake of evidence-based care for early OA and DMTs, by targeting the behaviours of both HCPs and their patients
^
48
^. Evidence based care is informed by clinical practice guidelines and focuses on patient education, exercise and promoting self-management
^
11,
15,
26
^. The KNEE-DEeP intervention will aim to ensure patients receive evidence based management and consistent information at an early point in their care from both the GP and physiotherapist, thereby reducing unnecessary referral to secondary care and inappropriate imaging. GPs and physiotherapists will receive specific training to deliver the patient intervention and enhance their skills and confidence in managing patients with this type of knee pain. Content and design of the HCPs training session will draw on evidence from a range of chronic musculoskeletal conditions
^
64–
69
^. The content of the intervention aligning to the Template for Intervention Description and Replication (TIDieR) guidelines is summarised in
Table 2
^
70
^.

**Figure 2. f2:**
[figure not shown]
KNEE-DEeP Intervention. * degenerative meniscal pathology or early osteoarthritis

**Table 2. T2:** Overview of KNEE-DEeP intervention delivery described according to the TIDieR guidelines.

	Item
1.	Brief name
	Knowledge Translation and Exercise for Degenerative Meniscal Pathology and Early Knee Osteoarthritis (KNEE-DEeP)
2.	Why
	Knee pain in people with degenerative meniscal pathology and early OA is frequently managed sub-optimally with underuse of evidence-based treatments like exercise and education, and overuse of orthopaedic referrals and advanced imaging. The KNEE-DEeP intervention was designed by integrating behavioural change theory with qualitative findings from clinicians and patients and adapted to the local health context. The intervention is targeted at both patients and health care professionals to improve the uptake of evidence-based care for patients with early knee OA and degenerative meniscal pathology.
3.	What (intervention procedures)
	(ii) GPs attend a 2-hour educational workshop on management of this type of knee pain and receive written educational resources. Physiotherapists attend a 2-hour training session supplemented with a pre-recorded webinar and written educational materials on delivery of the ’best practice’ physiotherapy session. Training content will be based on clinical guidelines for knee OA and degenerative knee disease and the wider musculoskeletal evidence base on self-management and parson centred care. (ii) Patient participants receive an ‘enhanced consultation’ from their GP. This constitutes a physical examination, key educational messages, a Patient Advice Leaflet “Understanding My Knee Pain”, a simple starter exercise programme, a management plan agreed with the GP and referral to the ‘best practice’ physiotherapy session. Patient participants also attend a 1-hour best practice physiotherapy session with a participating physiotherapist. The core elements of the session are (i) a clinical assessment (ii) an exploration of the patient’s beliefs and expectations about their knee pain (iii) tailored patient education on likely prognosis, beliefs about pain, physical activity, weight management and other lifestyle factors (iv) information on self-management skills such as load management, activity modification and monitoring pain response (v) completion of a goal and action plan worksheet (vi) provision of an exercise programme and/or physical activity plan.
3.	What (materials)
	GPs receive a study folder handbook detailing study procedures (e.g. recruitment, intervention delivery, referral to ‘best practice’ physiotherapy session). Educational materials will include copy of PowerPoint slides, communication tips, links to patient educational videos on weight maintenance, load management etc. Physiotherapists receive a training manual detailing components of the ‘best practice’ physiotherapy session, a pre-recorded webinar on addressing patient fears and misconceptions about their knee pain, and educational materials and self-management resources. Participating patients receive a Patient Advice Leaflet, with illustrated home exercises and video links, written exercise programme with progressions and regressions, a goal setting and action plan worksheet, physical activity logbook and additional educational handouts on management of flare-ups etc, as appropriate.
4.	Who provided
	Participating GPs deliver the ‘enhanced consultation’ to potential patient participants, while participating musculoskeletal physiotherapists provide the ‘best practice’ physiotherapy session. A clinical specialist physiotherapist and researcher ([name]) facilitates the training workshops to participating GP and physiotherapists, with support from clinical and academic physiotherapy colleagues.
5.	How
	Training workshops are delivered to GPs in small groups (n=6 to 8), either as in-practice training, or with several GPs practices together. Participating patients receive an ‘enhanced consultation’ during a routine consultation with their GP and the ‘best practice’ session will be one-to-one with the physiotherapist.
6.	Where
	The location for GP training varies, either in a GP practice or a rented meeting room to facilitate GPs from several practices. Physiotherapist training is held in the outpatient clinic of a physiotherapy department in a publicly funded hospital, where the ‘best practice’ physiotherapy intervention is delivered. GPs deliver an ‘enhanced consultation’ in their practice.
7.	When and how much
	Participating GPs and physiotherapists receive their respective 2-hour training workshop on enrollment into the study. Patient participants receive an ‘enhanced consultation’ with their participating GP when they present to their GP practice with knee pain. A single one-hour ‘best practice’ physiotherapy session is delivered within 2 weeks of the GP consultation.
8.	Tailoring
	Participating GPs are advised to individualise all aspects of their advice and education according to patients' presentation. Tailoring of patient education and individualised exercise prescription will be a key aspect of the physiotherapy intervention according to patients' goals and preferences.
9.	Modifications
	Any modifications will be reported.
10.	How well (planned)
	Participating GPs physiotherapists receive prior training in how to deliver the patient intervention. Fidelity checklists to self-assess their delivery are completed by GPs and physiotherapists. Participating patients complete a checklist of components of intervention received during the GP consultation.
11.	How well (actual)
	This will be reported in the primary paper.

OA, osteoarthritis; TIDieR, Template for Intervention Description and Replication.

**
*GP intervention.*
** The main components of the GP intervention are a training workshop to support the delivery of an ‘enhanced consultation’ for this type of knee pain, a Patient Advice Leaflet to support their consultation, and the facility to refer eligible patients to a ‘best practice’ physiotherapy session.

a)
**GP training workshops** are focused on training and supporting GPs to deliver an ‘enhanced consultation’ for knee pain. Training will be delivered in-person by the PI and supported by two experienced musculoskeletal physiotherapists. This 2-hour training session will cover; physical examination of the knee, clinical features of degenerative meniscal pathology and early OA, screening for serious pathology, appropriate use of imaging
^
27
^, information on evidence-based treatment options and exercise prescription. Tips on communicating effectively with patients and providing a diagnosis will be discussed. GPs will be introduced to four key educational messages to provide within the patient consultation, and how to use the Patient Advice Leaflet to prescribe some simple exercises. Other components of the ‘enhanced consultation’ including a physical examination and making a treatment plan will be outlined, along with the KNEE-DEeP study procedure. An online training session will be held to facilitate GPs unable to attend in-person. Training content will remain consistent by following a training manual and using PowerPoint slides. Workshops will be accredited by the Irish College of General Practitioners and GPs will receive Continuous Professional Development credits for attending. Study procedures around patient recruitment, along with additional information and resources for GPs to use with patients, will be provided in study folders provided to each individual GP.b)A
**Patient advice leaflet** (Extended Data, File F,
https://osf.io/fwy36/)
^
58
^ written in plain language will aim to support educational messages delivered verbally and provide the GP with a means to prescribe some simple ‘starter’ exercises. This bespoke educational resource designed with patient stakeholders will re-enforce key messages delivered verbally on diagnosis, prognosis and management. Knee exercises organised into three levels of difficultly are described in the leaflet and accompanied by a QR code linking to exercise videos.c)GPs will have the facility to refer eligible patients to an early
**‘best practice’ physiotherapy session**. GPs will complete a bespoke physiotherapy referral form and email to the Physiotherapy Department of UHK. The referral form (Extended Data, File G,
https://osf.io/fwy36/)
^
58
^ will prompt GPs to indicate that they have provided the components of an ‘enhanced consultation’ prior to making the referral. An in-person physiotherapy appointment will follow within two weeks. The components of the GP ‘enhanced consultation’ and the content of the ‘best practice’ physiotherapy session are described below.

**
*Physiotherapy intervention.*
** This intervention for participating physiotherapists consists of training and provision of educational resources to support the delivery of the ‘best practice’ physiotherapy session.

a)A
**physiotherapist training workshop** will be delivered by two members of the research team ([name] and [name]). This two-hour session will include review of knee joint assessment, exploring individual patient beliefs and expectations about their knee pain, delivering tailored patient education, exercise prescription, self-management skills and techniques to maximise patient adherence to a management plan. The workshop will focus on training physiotherapist to adopt a collaborative approach during the ‘best practice’ session that focuses on listening to the patient, understanding their individual concerns and worries, delivering information to reduce fear and address misconceptions, before designing a plan focused on their own goals and interests and delivering tailored education and an exercise programme. This session will be accompanied by a training manual to ensure standardisation of training and material delivered. While training content for clinicians is standardised, physiotherapists will be encouraged to individualise the patient sessions. In addition to the training workshop, physiotherapists will listen to a thirty-minute pre-recorded webinar on addressing common patient misconceptions and beliefs about knee pain. The training manual will include written guidance on the core components of the ‘best practice’ session and additional educational resources on knee pain and communication tips.

**
*Patient intervention.*
** The patient intervention consists of an ‘enhanced consultation’ with their GP and a ‘best practice’ physiotherapy session delivered within two weeks of their GP visit. The patient intervention will be guided by clinical guidelines and include education, exercise and where appropriate, weight management advice
^
26
^. A core focus will be boosting self-management skills and empowering patients with information and resources to manage their symptoms, without the need for inappropriate imaging or surgical consultations. These intervention components will be delivered briefly during the GP consultation through verbal and written information, and addressed more comprehensively during the physiotherapy ‘best practice’ session and using printed and video resources.

a)The ‘
**enhanced consultation’** with the GP consists of four components; (i) a clinical assessment, (ii) verbally delivered educational messages, (iii) a Patient Advice Leaflet and (iv) a documented treatment plan between the GP and patient. The key educational messages relate to providing a diagnosis, setting positive realistic expectations about prognosis, the safety and benefits of exercise for the knee, and tips for long-term knee health including, as appropriate, weight maintenance or weight loss (Extended Data, File H,
https://osf.io/fwy36/)
^
58
^. GPs guidance on the consultation will be to provide reassurance to patients through a thorough clinical examination and providing a broad diagnosis for knee pain that draws on the patient history and potential risk factors, rather than a narrow focus on structural pathology. Encouraging positive patient attitudes about the role of exercise prior to attending the physiotherapy session is another important tenant.b)The early
**‘best practice’ physiotherapy** session is a single face-to-face appointment with a participating physiotherapist in the Physiotherapy Department. This single session is not designed to replace usual physiotherapy care, rather it aims to re-enforce the brief educational messages delivered by the GP and empower the patient through education and self-management skills to take early and positive steps towards their own recovery. The structured one-hour session with the physiotherapist will include the following core elements (i) a clinical assessment (ii) an exploration of individual patient beliefs and expectations about their knee pain and addressing misconceptions (iii) provision of individualised patient education on likely prognosis, beliefs about pain, physical activity, weight management and other lifestyle factors (iv) education on self-management skills such as load management, activity modification and monitoring pain response (v) completion of a goal and action plan worksheet. Patients will collaboratively identify specific personalised goals and targets with the physiotherapist and develop a linked action plan that includes a home exercise programme and /or a physical activity plan. Exercises are selected from a menu (Extended Data, File I,
https://osf.io/fwy36/)
^
58
^ that includes simple starter exercises and more advanced exercises. Organised into three levels of difficulty, these exercises target the hip and knee muscles and will be selected according to individual patients goals and preferences. Guidance will be provided on progressing and regressing individual exercises. Participants will be encouraged to use a physical activity logbook to self-monitor progress and adherence. Depending on their educational needs they may receive additional written resources (e.g managing flare-ups).Having availed of the study intervention, it will be at the discretion of the patient and their GP whether to arrange for further physiotherapy, either public or private, depending on the accessibility of their local services. The physiotherapist delivering the ‘best practice’ session can make a recommendation to the GP on the discharge summary. Any further treatment the patient avails of will be recorded by the follow-up patient questionnaires. During the 6-month follow-up period, patients can contact their physiotherapist over the phone for further advice or sign-posting.

